### 13.0 Recruitment Methods

13.1 All potentially eligible patients treated for pilonidal disease at NCH, OSU, or one of the community pediatric practices will be informed of the study. All potential patient recruitment sites will have flyers and pamphlets advertising the study. Study team members will contact sites monthly to answer questions and provide additional information and study related materials as needed. Clinic schedules will be reviewed by members of the research team and providers seeing patients with pilonidal disease will be asked if they can be approached about the study. Nurses in each of the clinics will be informed of the study and inform patients about the study and provide study contact information to the patient and their family. In addition, they will ask the patient and family if they would like additional information on the study. If they do want more details, they will ask for permission to provide their contact information to the study team. Subsequently, a trained member of the research team will contact the patient and family to assess their eligibility against both inclusion and exclusion criteria. If all eligibility criteria are met, the patient and legal guardian (if < 18 years of age) will be invited to enroll. The research team member will review the information about the study and answer any questions. If they remain interested in enrolling, they will be scheduled for a clinic visit. At the initial clinic visit, a trained member of the research team will review the study protocol and procedures and the risk and benefits of each treatment with the patient and caregiver again, answer any additional questions, and written informed consent and assent (for patients < 18 years of age) will then be obtained.

If a patient is enrolled into the study at a telehealth visit, a trained member of the research team will contact the family to obtain phone or electronic-consent. At the end of the telehealth video visit, if the patient verbally states they are interested in the study, a trained member of the study will join the telehealth call through EPIC by invite of the principal investigator. The trained member will review the study protocol and procedures and the risk and benefits of each treatment with the patient and caregiver, answer any questions, and phone/ electronic-consent and assent (for patients < 18

PROTOCOL TITLE: A randomized controlled trial of laser hair depilation in adolescents with pilonidal disease

years of age) will then be obtained. If the patient uses electronic-consent, it will be given via REDCap. A signed copy of the consent will be sent to the patients. Due to COVID-19 restrictions, there may be a delay in mailing the signed consent forms. However, when social restrictions are lifted and staff are able to access the necessary resources, the consent will be mailed.

13.2 The study will be conducted at Nationwide Children's Hospital (NCH). Study participants will be recruited in the NCH surgery clinic (in-person or through telehealth), ED, inpatient units and by phone (for patients interested in the study from The Ohio State University Wexner Medical Center, community pediatric and adult practices, emergency rooms and urgent cares, community recreation boards, local colleges, local high schools, Columbus City Schools, and all those employed or seeking care through the NCH network – see Section 13.3).

13.3 All potentially eligible patients treated for pilonidal disease at NCH, The Ohio State University Wexner Medical Center (OSU), or one of the community pediatric and adult practices will be informed of the study. Potential participants may also be identified through numerous outreach efforts conducted through brochures and flyers made available at emergency rooms and urgent cares, community recreation boards, local colleges, local high schools, Columbus City Schools, and all those employed or seeking care through the NCH network.

If interested, their names and contact information will be sent to the research team at NCH by a provider or referral source or those receiving study information via one of the informational outlets will contact a member of the study team directly for additional information.

In addition, a bi-monthly automated data report will be generated for the study staff to help identify all patients seen in the NCH network and at The Ohio State University Wexner Medical Center with a diagnosis of pilonidal disease. Potential candidates identified through these data reports will be sent a letter and brochure describing the study and contact information via snail mail.

As part of OSU Wexner Medical Center Recruitment, this study has been invited to participate in a recruitment effort through OSU's MyChart Portal.

Ohio State's digital health portal, MyChart, is a system that enables patients to connect with their healthcare providers and manage their health information through a variety of interactive functions. The MyChart Recruitment function is a new recruitment approach for researchers that operates through the MyChart message inbox. This recruitment approach will limit unnecessary study communication by targeting messages to patients that are eligible based on study inclusion criteria. This message will allow the patient to express interest in study to allow for a research

PROTOCOL TITLE: A randomized controlled trial of laser hair depilation in adolescents with pilonidal disease

851 team member to make contact with them, contrarily, the patient also has  
852 the opportunity to decline subsequent information, at which time no  
853 further contact will be made with that patient concerning the study. Our  
854 study has been selected as one of four pilots for the launch of this function  
855 in the beginning of February.

856 In addition to the automated, introductory message, the potential  
857 participant will receive an attached description of the study protocol (study  
858 message). This messaging can be found in the appendix attached.

859 Here is how we will identify and notify potential study participants  
860 through OSU MyChart Recruitment:

861 i. All the PHI that is required for the study – eg: MRN, MyChart User or  
862 Not, Phone number, Home Address, Email Id, Contact Info,  
863 Demographics, Medication, Labs, Any Dates of interest etc.

864 MRN, Name, Phone Number, MyChart User or Not, Home Address,  
865 Email ID, Age, Race, Ethnicity, Gender, Insurance Coverage Status,  
866 Socioeconomic Data, Medications, Labs, Medical History Related to  
867 Pilonidal Disease, Family History of Pilonidal Disease, Current Pilonidal  
868 Disease Symptoms, Physician Office Visit, Emergency/Urgent Care Visit,  
869 Inpatient Visits for Pilonidal Disease (Same PHI for non-MyChart Users  
870 defined in aforementioned sections of protocol).

871 ii. The conditions/eligibility criteria to identify cohort.

872 Eligibility criteria include patients with:

873 Fitzpatrick skin types, 11-21 years of age, and a previous diagnosis and  
874 treatment for active pilonidal disease. To identify the cohort through OSU  
875 MyChart, patients will be identified in the query through the Information  
876 Warehouse that fit the study inclusion criteria by an Honest Broker. The  
877 query will include a combination of CPT codes and ICD-10 codes listed as  
878 follows:

879 ICD-10 Codes: LO5.01, LO5.02, LO5.91, LO5.92

880 ICD-10-PCS Codes: 0H96XZZ, 0JB90ZZ, 0H98XZZ, 0HX8XZZ

881 CPT Codes: 01999, 10090, 10081, 11770, 11771, 11772, 88304

882 iii. A list of MRNs (obtained through IW) will go directly to Research  
883 IHIS team ([name]) and the Research IHIS team will use the  
884 identified MRNs to send messages via MyChart . This list of patients and  
885 their contact information will also be shared with the NCH study team so  
886 an additional letter can be sent to the patient's home to notify them that  
887 they may be eligible for our study.

888 iv. (Only) For the Patients who said "Contact Me" (accepted) the medical  
889 record will be viewable by study team.

890 v. Script (written or spoken) to be the used for communications through  
891 MyChart with interested patient. Each message sent through MyChart is  
892 automatically introduced with the following message by the system:

893 A computer-generated search found that you may fit the study described  
894 below. Unless you decide to click interested in this research opportunity,  
895 no one on the research team will know that you have been contacted. Your  
896 privacy and your health are most important to us. The Ohio State Wexner  
897 Medical Center is driven by our mission “to improve people’s lives  
898 through innovation in research, education, and patient care.

899 If the patient indicates that he/she is interested in the study, a research  
900 member will reply to the patient with: Thank you for your interest in the  
901 Pilonidal Laser Hair Removal Study. A trained member from our research  
902 team will be in contact with you shortly to discuss the details of the study  
903 and answer any questions or concerns you may have. If there is a preferred  
904 contact number, you may reply to this message with that information. If  
905 not, we will use the preferred contact information found in your chart. We  
906 look forward to talking to you soon. Thank you.

907 Pilonidal Research Team

908 Subsequently, a member of the research team will contact all identified  
909 patients received via data report, provider referral, and outreach outlets to  
910 assess their eligibility against both inclusion and exclusion criteria. If all  
911 eligibility criteria are met, the patient and legal guardian (if < 18 years of  
912 age) will be invited to enroll. The research team member will review the  
913 information about the study and answer any questions. If they remain  
914 interested in enrolling, they will be scheduled for a clinic visit. At the  
915 initial clinic visit, a member of the research team will (1) review the study  
916 protocol and procedures; (2) explain the risk and benefits of each  
917 treatment; (3) answer questions; and (4) obtain written informed consent  
918 and assent (for patients 11-17 years of age). All of the enrollment  
919 materials have been reviewed by patients, families, pediatricians, and  
920 surgeons to ensure that they are balanced representations of the risks and  
921 benefits of each treatment option. These materials have been tailored for a  
922 Flesch-Kincaid reading level between the 5th and 6th grade to ensure that  
923 both children and low-literacy adults are able to understand them. In  
924 addition, we have attempted to minimize the effects of differences in  
925 numeracy by presenting numbers, percentages, and proportions  
926 graphically using figures to facilitate understanding. A member of the  
927 research team will be available by pager 24 hours per day to answer and  
928 address study-related questions from patients, families, and referring  
929 medical providers.

930 13.4 All potential patient recruitment sites will have flyers and  
931 pamphlets advertising the study. See attached marketing documents.

932 13.5 *Describe the amount and timing of any payments to subjects.*

## **14.0 Withdrawal of Subjects\***

14.1 If the Principal Investigator believes that this study is not good for the participant, the study instructions are not followed, participation in the study may be stopped. If unexpected medical problems come up, the Principal Investigator may decide to also withdraw the participant from the study.

14.2 Participants and their legal guardian have the right to switch to the standard treatment and/or withdraw from the study at any time. Withdrawal from the study will not affect receipt of clinical care. If the participant is terminated, the study will contact the participant and inform them,

14.3 If the participant withdraws participation study members will ask permission to retain authorization of the use of their PHI. If they want to revoke that permission then they must request this in writing to the PI at Nationwide Children's Hospital, [name]. If the participant withdraws their authorization, no new PHI will be collected and the PHI already collected will not be used unless it has already been used or is needed to complete the study analysis and reports.

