## **4.0 Study Endpoints**

4.1 The primary outcome is the rate of recurrent pilonidal disease at 1 year defined as development of a new pilonidal abscess, folliculitis, or draining sinus after treatment, which would require antibiotic treatment, additional surgical incision and drainage, or excision within 1 year of enrollment.

Secondary outcome include: differences in disability days of the patient at 1 year, disability days of the caregiver at 1 year, HRQOL, health care satisfaction, disease-related attitudes and perceived stigma, rates of

PROTOCOL TITLE: A randomized controlled trial of laser hair depilation in adolescents with pilonidal disease

pilonidal disease-related complications, rates of pilonidal disease related procedures (incision and drainage), surgical excision, and post-operative complications, and rates of compliance with recommended treatment.

A summary of the outcomes that will be assessed are listed in the table below (Table 2).

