## **17.0 Data Management\* and Confidentiality**

17.1 The means/medians and standard deviations/interquartile ranges of the prognostic variables will be evaluated in the total study sample and will be compared between groups using t-tests or Mann Whitney U tests for continuous variables and chi-squared tests for categorical variables. For the primary outcome of recurrence within one year, we will calculate this proportion and its 95% confidence interval, based on the exact binomial distribution, in both treatment groups and compare this proportion between groups using a Chi-squared test.

Other outcomes will be compared using chi square tests, if categorical, and t-tests or Mann Whitney U tests as appropriate if continuous. In analyses that include outcome data collected after patients in the control group were offered laser treatment, both intention-to-treat and per-protocol analyses (with control group patients analyzed according to the treatment they received and according to the time from the start of their laser treatment) will be performed. SAS Enterprise Guide (Cary, NC) will be used for the statistical analyses.

The sample size needed to assess the primary outcome of the proportion of patients with recurrent pilonidal disease at 1-year is based on: 1) previous published studies and institutional data on the recurrence rates of pilonidal disease and 2) the efficacy of laser hair depilation treatment to reduce pilonidal disease recurrence in previous studies and our institutional pilot study. In this RCT, the recurrence rate within 1 year is expected to be 12% in the control group and a maximum 2% in the laser group. Based on these estimated recurrence rates, under a group sequential design with one interim and one final analysis, an overall type I error rate (two- sided) of 5 % and power of 80%, the sample size required for this trial is 122 patients in each treatment group. Assuming a 10% drop out rate over the course of the 1 year follow-up, we will plan to enroll 136 patients in each group (total; n=272 patients). The total of patients increased to 302 due to reasons related to COVID described above.

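### Section 14.1 allows study participation to be ended for not following instructions, and nothing requires 12-month outcome collection to continue or such patients to be kept in the 1-year comparison as randomised

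*Combined protocol and SAP*

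**What the plan says.** Section 14.1 gives the investigator discretion to end participation on several grounds. One is that "the study instructions are not followed, participation in the study may be stopped". Its next sentence speaks of withdrawing the participant from the study, so the rule concerns the study and not just the laser sessions.

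Section 14.2 gives families the "right to switch to the standard treatment and/or withdraw from the study at any time". For investigator-initiated termination it adds only this: "If the participant is terminated, the study will contact the participant and inform them". It does not mention outcome follow-up.

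Section 14.3 deals with participants who withdraw themselves. Here "study members will ask permission to retain authorization of the use of their PHI", and the only express end to data collection is this: "If the participant withdraws their authorization, no new PHI will be collected".

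Section 4.1 states: "The primary outcome is the rate of recurrent pilonidal disease at 1 year". Its list of secondary outcomes ends "and rates of compliance with recommended treatment". Table 2 schedules compliance at every time point.

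Section 17.1 compares 1-year recurrence by a chi-squared test, with no stated analysis set and no rule for missing outcomes. Intention-to-treat appears only here: "In analyses that include outcome data collected after patients in the control group were offered laser treatment, both intention-to-treat and per-protocol analyses".

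Section 17.2 says that participants and the research team know the allocation. Section 6.4 has laser patients complete the month 1 to 4 surveys in person, and controls by phone, email or web unless they book a visit.

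**The concern.** Non-adherence arises after randomisation. The protocol's own rationale (section 6.2) is that continued hair removal prevents recurrence, so adherence is plausibly related to the primary outcome. A discretionary rule that ends participation for non-adherence, with no requirement to keep collecting outcomes, opens a route to informative loss.

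Two features of this trial add to the risk. Staff apply the rule knowing the allocation. Non-attendance at a laser visit is seen directly, while a control patient who stops removing hair is known mainly from self-report. The two arms could therefore lose different numbers and kinds of patients.

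Nothing downstream repairs this, because section 17.1 does not commit the 1-year comparison to all randomised patients as assigned. For the compliance outcome, the patients whose later answers would be missing are those who complied least.

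**Working it through.** **Is there a safeguard elsewhere?**

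| Provision | Whom it covers | Does it cover a patient terminated under 14.1? |
|---|---|---|
| 14.2, notice of termination | Terminated participants | They are informed; follow-up is not mentioned |
| 14.3, retained authorization | Participants who withdraw themselves | Not addressed |
| 6.4, primary care contact at 12 months | Patients who do not respond | Not addressed |
| 6.4, COVID surveys without treatment | Patients whose treatment is delayed, with a signed addendum | No |
| 17.1, intention-to-treat | Analyses with data after the laser offer to controls | Not for the 1-year comparison |

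No provision requires follow-up of these patients, and none excludes it.

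**The plan's sample size.** Section 12.1 assumes 12% vs 2%, two-sided 5%, power 80%, and gives 122 per group.

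- Without continuity correction: n = [1.960·√(2·0.07·0.93) + 0.842·√(0.12·0.88 + 0.02·0.98)]² / 0.10² = (0.707 + 0.298)² / 0.01 ≈ 101.0, rounded up to 102.
- With continuity correction: (101.0/4)·[1 + √(1 + 4/(101.0·0.10))]² ≈ 120.2, rounded up to 121, close to 122.
- Dropout: 122 / 0.90 = 135.6, rounded up to 136, as stated.

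The sample size is not in error on this point.

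**How far could removal move the comparison?** The documents give no rate of withdrawal for non-adherence, so these inputs are assumptions:

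- q = share of an arm removed with no outcome data, 5 to 20%. All non-adherers are taken to be removed.
- k = recurrence rate of non-adherers divided by that of adherers, 1 to 3.
- p = true rate of the whole arm, 12% control and 2% laser from section 12.1, or 12% in both for the case of no effect.

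Since p = (1 − q)·r + q·k·r, where r is the adherers' rate, the observed rate after removal is r = p / [1 + q(k − 1)].

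Example: 20% of control and 5% of laser removed, k = 3. Control: 12/1.4 = 8.57%. Laser: 2/1.1 = 1.82%. Difference: 6.75, or about 6.8 points.

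| Removed, control / laser | k | Observed, true 12% vs 2% | Difference (points) | Spurious difference, control minus laser, true 12% in both |
|---|---|---|---|---|
| Any | 1 | 12.0% vs 2.0% | 10.0 | 0 |
| 10% / 10% | 2 | 10.9% vs 1.8% | 9.1 | 0 |
| 10% / 10% | 3 | 10.0% vs 1.7% | 8.3 | 0 |
| 20% / 5% | 2 | 10.0% vs 1.9% | 8.1 | −1.4 |
| 20% / 5% | 3 | 8.6% vs 1.8% | 6.8 | −2.3 |
| 5% / 20% | 2 | 11.4% vs 1.7% | 9.8 | +1.4 |
| 5% / 20% | 3 | 10.9% vs 1.4% | 9.5 | +2.3 |

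Under the planned effect, every row with k above 1 shrinks the difference. In this model it could exceed 10 points only if the share removed from the laser arm were more than six times that from control (the ratio 12/2). A spurious gain for laser appears here only when the true rates are equal and laser loses more.

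**The case against.** The strongest reply is that 14.1 is permissive and does not say that outcome collection stops, while 14.3 expressly ends new collection only when authorization is withdrawn. Other parts of the plan look built to keep non-adherers in. Compliance is asked at every visit, the sample questionnaire records non-use of both methods, surveys may continue through COVID treatment delays, and outside records are sought. The term for study instructions is also undefined. All of this stands, and it limits the point to a risk that the text leaves open. It does not supply the missing requirement.

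A reader might infer more than the documents support:

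- *That patients are in fact dropped and the result is biased.* Nothing shows that the rule has been used. Section 12.1 reports about 15 laser patients without data, which shows that loss tied to receiving treatment can occur. They arose from COVID delays, not through 14.1.
- *That 14.2 merges switching treatment with leaving the study.* Its wording allows either one or both.
- *That the laser rate is understated by 1 to 3.6 points.* This takes 2% as the adherers' rate: (1 − f)·2% + f·r gives 3.0% or 4.0% for f = 10% or 20% at r = 12%, and 3.8% or 5.6% at r = 20%. Section 12.1 gives 2% as the maximum for the whole laser group. Holding the arm at 2% with the same 6:1 ratio of risks (12% to 2%), removal leaves 2/1.5 = 1.33% or 2/2 = 1.0%, an understatement of 0.7 to 1.0 point. The reading also removes nobody from control.
- *That the compliance rate is wrong by construction.* Answers given before withdrawal remain. What is lost is the later time points.
- *That removals come straight off the 122 evaluable per arm.* The plan already allows 10% dropout. That allowance covers numbers, not informative loss.

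**Conclusion.** The point holds as a gap in a stated rule, and the sponsor should close it. Section 14.1 permits ending study participation for not following instructions. No section then requires 12-month outcomes to be collected, and none commits the 1-year comparison to all patients as randomised. If the rule is used, it can bias the recurrence comparison, and it leaves compliance data incomplete for the least compliant patients.

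The size and direction of any bias are not known from the documents. The observed range of about 6.8 to 10.0 points against a planned 10, and the spurious difference of 0 to about 2.3 points either way, rest on the assumed 5 to 20% removal per arm, a risk ratio of 1 to 3, and removal of every non-adherer with no outcome data. The bias is zero if non-adherence is unrelated to recurrence. A bias in favour of laser is possible but not established.

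**What to change.** - **Section 14.1:** remove not following study instructions as a ground for ending study participation, meaning follow-up. State that patients who stop, miss or switch study treatment, for whatever reason, stay in the scheduled surveys, the record requests and the existing 12-month primary care contact, unless they withdraw consent or authorization.
- **Sections 14.1 and 17.1:** state that these patients are analysed at 1 year in the arm to which they were randomised.
- **Section 14.2:** record stopping or switching treatment separately from withdrawal from follow-up, each with date and reason.

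This changes who is followed and analysed. It proposes no change to any clinical rule for stopping treatment, and it does not extend primary care contact beyond month 12.

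The cost is an edit to these sections and one added form field; the calls and record requests are already planned. If the consent form repeats the 14.1 rule, it needs the same edit. The downside is that the laser rate may look slightly less favourable with non-adherent patients kept in.
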